##### Control Group

In the control group, routine nursing care and current health education content will be provided, including the following: introduction to the department’s environment, rules, and regulations; admission counseling; examination guidance; ongoing education on daily care, medication management, and health practices during hospitalization; proactive support and communication by medical staff, including resolving questions and sharing caregiver experiences; and discharge instructions with follow-up schedules for chemotherapy (Multimedia Appendix 3).

Participants in the control group will be offered an FCEM-based intervention regimen on their second admission (at the beginning of the second course of treatment), which will be appropriately adapted to the control group’s second chemotherapy treatment.

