##### Follow-Up Assessment

To evaluate the sustained impact of the intervention, an additional follow-up will be conducted 1 month after discharge. This will be completed via telephone and web-based questionnaire by the research assistants. The same validated instruments used during hospitalization will be used to measure caregiving preparedness, caregiving capacity, self-efficacy, and depression, anxiety, and stress.

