### Ethical Considerations

This study was approved by the Ethical Review Committee of West China Second Hospital of Sichuan University (approval number YXKY2024432). The trial was registered on February 5, 2025, with ClinicalTrials.gov (NCT06810388). Before data collection, the study leader will obtain written informed consent from all participants. Participants will also be informed in advance that they will be contacted for a follow-up assessment approximately 1 month after discharge.

During the study, personal information, such as names, gender, and other identifiers of participants and their children, will be replaced with codes or numbers to maintain confidentiality. Access to this information will be limited to authorized researchers, ensuring the privacy of participants and their children is fully protected. While the study results may be published in academic journals, no personal details of the participants will be revealed.

All participants will be informed of their right to withdraw from the study at any time and that completing the questionnaire will not affect their children’s medical or nursing care. All family caregivers in the control group will be asked if they would like to receive the family empowerment intervention program upon their second admission, which the researchers will provide.

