## Results

### Recruitment Progress

The study was approved by the Ethical Review Committee of West China Second Hospital of Sichuan University on January 9, 2025 (approval number YXKY2024432). We plan to recruit participants for the control group from July to December 2025. We will recruit caregivers for the intervention group from July to December 2026. Data collection will occur throughout the recruitment period. Results are expected to be published in late 2027.

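### Controls are offered the FCEM programme at second admission, and nothing in the text requires their 1-month follow-up to come first

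*Protocol article*

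**What the plan says.** **The offer to controls.** The protocol article, under Control Group, says: "Participants in the control group will be offered an FCEM-based intervention regimen on their second admission (at the beginning of the second course of treatment". Setting and Participants makes the same promise. Ethical Considerations adds that all control caregivers "will be asked if they would like to receive the family empowerment intervention program upon their second admission", and that the researchers will provide it. The offer is therefore open to every control and voluntary.

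**The late assessment.** Follow-Up Assessment says: "To evaluate the sustained impact of the intervention, an additional follow-up will be conducted 1 month after discharge". It continues: "The same validated instruments used during hospitalization will be used to measure caregiving preparedness, caregiving capacity", and lists the remaining outcomes. I read the discharge in question as the one that ends the first admission.

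**The earlier assessment and the waves.** The post-intervention questionnaire is given 3 days before discharge from the first admission (Setting and Participants). Recruitment Progress says: "We plan to recruit participants for the control group from July to December 2025". The intervention wave is the same six months of 2026.

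**Handling of exposure.** Data Analysis removes from the primary analysis those who ask to move to the other group by preference. It does not mention controls who take up the planned delayed offer.

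**Not in the text.** The article does not give the interval between first discharge and second admission, the expected uptake, or any rule on which of the two events comes first.

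**The concern.** Two clocks run from a control child's first discharge. One leads to the 1-month questionnaire, the other to the second admission and the offer of the programme. They are not tied together. A control who returns within about a month and accepts can receive the study intervention before the assessment at which that caregiver stands for usual care.

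If the programme works, such controls move towards the intervention group and the 1-month difference shrinks. The control group's own change from baseline to 1 month is altered too. The stated purpose of this assessment is "To evaluate the sustained impact of the intervention", so the risk is a false conclusion that the effect has faded, when in fact the comparator has been partly treated.

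**Working it through.** **1. The plan's own figure.** Setting and Participants gives α = 0.05, power 0.8, effect size 0.5, 128 caregivers, and 142 after 10% loss. A two-sided two-sample t test (noncentral t) with these inputs needs 63.8, so 64 per arm and 128 in total. Then 128 / 0.9 = 142.2, against the stated 142. The sample-size figure reproduces and is not in question; 64 evaluable per arm is used below.

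**2. Order of events for one control.** Let D be the day of first discharge and h the number of days from D to second admission.
- Post-test: D − 3.
- Offer of the programme: D + h.
- Follow-up: about D + 30.

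Because h is positive, the post-test always precedes a control's own exposure. The follow-up precedes it only if h exceeds about 30. The text gives no h and no rule that fixes the order.

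**3. Size at 1 month.** Let f be the share of the between-group contrast lost. It is the product of three quantities that the article does not state: the share of controls readmitted before follow-up, the share of those who accept, and the share of the full effect which that exposure carries. For example, if half of the controls are exposed and each gains half of the effect, f = 0.5 × 0.5 = 25%. The remaining difference is d = 0.5 × (1 − f), and the noncentrality is d × √(64/2).

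| f (assumed) | Remaining d (SD) | Noncentrality | Power, 64 per arm | Evaluable per arm for 80% power |
|---|---|---|---|---|
| 0 | 0.500 | 2.83 | 0.80 | 64 |
| 10% | 0.450 | 2.55 | 0.71 | 79 |
| 25% | 0.375 | 2.12 | 0.56 | 113 |
| 50% | 0.250 | 1.41 | 0.29 | 253 |
| 75% | 0.125 | 0.71 | 0.11 | 1006 |

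These rows apply to a between-group comparison at 1 month only.

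**4. Overlap with the control wave.** July to December has 184 days. Assume uniform admissions and a gap of g days from first to second admission. The share of controls whose second admission falls inside the wave is (184 − g) / 184: 156/184 = 84.8% for g = 28, 124/184 = 67.4% for g = 60, and 94/184 = 51.1% for g = 90. It reaches zero only at about six months. So for gaps well short of six months, the programme could be delivered to returning controls while later controls are still being enrolled. This shows opportunity for spillover, not that spillover occurs.

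**The case against.** **What stands.** The programme is offered, not imposed, and neither uptake nor the interval between courses is given, so the number of controls exposed before follow-up cannot be computed. The shares in the table have no source in the document. The upper rows for f may also be too pessimistic, since controls would receive an adapted version early in a second admission, while the programme is built as staged sessions through a stay. The article calls the 1-month assessment additional and does not say outright that the groups will be compared there; an analysis within the intervention group would be untouched. Figure 1, the participant timeline, is not shown in the copy reviewed and may indicate an order.

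**What does not.** None of this supplies an ordering rule in the text. A statement about sustained impact in a two-group study invites a comparison with controls, and that comparison depends on an interval the plan leaves uncontrolled.

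**A stronger reading.** A reader might infer that the whole comparator is contaminated, including the pre-discharge comparison, because returning controls could share a ward, nurses or conversations with controls enrolled later. The documents do not support that. A control's own crossover always falls after that control's post-test. The study has a single centre (Limitations), and routine control care includes sharing of caregiver experiences (Control Group), so indirect spread is possible. But Ethical Considerations says the researchers will provide the delayed programme, and nurse delivery is described only for the intervention group. Nor does the article say why the groups were separated by calendar period, so it cannot be said that this purpose is defeated.

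**Conclusion.** The point holds for the 1-month assessment. The text lets controls receive the intervention before the follow-up at which they serve as comparator, and it has no rule for those who do. If some are readmitted within about a month and accept, any between-group comparison there is biased towards no difference, provided that the programme works. The size is illustrative: power falls from 0.80 to 0.56 at a 25% loss of contrast, to 0.29 at 50% and to 0.11 at 75%. If follow-up always precedes exposure, there is no loss through direct crossover.

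The pre-discharge comparison is not affected by a control's own crossover. Spillover to later controls in the 2025 wave is possible but not demonstrated, and no figure can be put on it. This should be changed, but it does not undermine the in-hospital comparison.

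**What to change.** Reconcile Setting and Participants, Control Group, Follow-Up Assessment and Ethical Considerations so that the order is fixed:

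- In both waves, complete the follow-up questionnaire at 1 month after discharge or immediately before any second-course FCEM session, whichever comes first. The article describes no such session for the intervention group, so name the matching point there (the second admission) to keep timing comparable.
- Record the date of each follow-up assessment and of any FCEM exposure.
- Make the between-group follow-up comparison on pre-exposure assessments, with a sensitivity analysis for the time from discharge to assessment. State how many control assessments were taken after exposure.
- Record FCEM deliveries to returning controls during the control wave, so that possible spillover can be described.

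The cost is some protocol and consent wording and a few date fields. Follow-up will be shorter than 1 month for some caregivers, which weakens the claim about durability for them.

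I would not require the offer to be postponed until the control wave has ended. On the overlap figures above, that could defer the promised second-admission offer for half or more of the controls, to guard against a spillover that the documents do not show.

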##### Follow-Up Assessment

To evaluate the sustained impact of the intervention, an additional follow-up will be conducted 1 month after discharge. This will be completed via telephone and web-based questionnaire by the research assistants. The same validated instruments used during hospitalization will be used to measure caregiving preparedness, caregiving capacity, self-efficacy, and depression, anxiety, and stress.

### Data Analysis

Data will be analyzed using SPSS version 26.0 (IBM Corporation). For general information, measurement data conforming to a normal distribution will be described by means and SDs, and count data will be described by frequencies and constitutive ratios. Missing data will be removed and will not be included in the analysis. Participants who request to switch groups based on their preferences will be excluded from the primary analysis; however, we will summarize the baseline characteristics of these participants and compare them to those who remain in their originally assigned groups. This comparison will include demographics to assess the potential impact of nonrandom attrition on study validity.

Independent-sample *t* tests will be used to compare caregiving preparedness, caregiving capacity, self-efficacy, and depression, anxiety, and stress scores between the 2 groups before the intervention. After the intervention, both within-group and between-group differences in these variables will be analyzed using independent-sample *t* tests, paired *t* tests, Mann-Whitney tests, and paired rank-sum tests.

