## Methods

### Data Collection

#### Setting and Participants

This is a quasi-experimental study. This protocol is version 1.0, finalized on July 8, 2025. We will select children with malignant tumors and their family caregivers who were hospitalized at West China Second Hospital, Sichuan University, between July 2025 and December 2026. Family caregivers of the children will be enrolled. The researchers will provide a detailed description of the study’s purpose and content to the participants, who must sign an informed consent form.

The QR code for the web-based questionnaire will be distributed after caregivers provide informed consent. The family caregivers recruited for the study will be divided into control and intervention groups. Children will be grouped according to their diagnosis and treatment timeline as follows: children admitted from July to December 2025 will form the control group, and those admitted from July to December 2026 will form the intervention group. The caregivers of the children will be enrolled along with the children. In the intervention group, the intervention program will be implemented after inclusion. For the control group, where routine health promotion is implemented, an intervention program based on FCEM will be offered upon the second admission to the hospital (Figure 1).

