**Figure 1 figure1:**
[figure not shown]
Participant timeline.

After the family caregivers complete the baseline survey, the researchers will distribute paperwork or provide verbal health promotion with relevant health promotion components and assess the caregivers’ knowledge weekly.

The questionnaire will be re-administered 3 days before the child is discharged. One researcher will enter the data, which will be double-checked for errors by another researcher. After all data are entered, the analysis will be performed by a designated specialist who remains unaware of the groupings. Finally, 2 additional researchers will independently review the analyses to ensure accuracy. Family caregivers will be aware of their grouping. If family caregivers prefer to adjust their groupings, appropriate adjustments will be made based on their identified needs.

The inclusion criteria are as follows: (1) children aged 0-18 years, (2) children clinically diagnosed with malignant neoplasms, and (3) first-time visitors to our hospital.

The exclusion criteria are as follows: (1) children diagnosed and treated with radiotherapy or chemotherapy in other hospitals and (2) children undergoing their first treatment in our hospital for recurrence of the disease.

Primary caregiver inclusion criteria are as follows: (1) the caregiver is enrolled along with the child, (2) the caregiver is aged 18 years or older, (3) the caregiver is a member of the child’s immediate family, (4) the caregiver has cared for the child for the longest period among multiple caregivers, (5) the caregiver has basic communication and reading skills and is proficient in Chinese, and (6) the caregiver has no previous history of psychiatric illness or consciousness-related disorders.

The sample size was calculated to be 128 using G*POWER 3 software [10] with the parameters α=.05, 1 – β=0.8, and effect size=0.5. Considering a 10% lost-to-follow-up rate, the total sample size required was estimated to be 142, with 71 caregivers in the intervention group and 71 in the control group.

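### Deletion is the only stated rule for missing data and is paired with unadjusted tests, so the group difference can be biased if loss differs between the two cohorts; the 1-month assessment is not named in the analysis

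*Protocol article*

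**What the plan says.** All places are in the protocol article.

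- **Missing data (Data Analysis).** The whole rule is "Missing data will be removed and will not be included in the analysis". It does not say whether removal is per participant, per scale or per test.
- **Switchers (same section).** Caregivers who ask to change group are left out of the primary analysis. Their baseline characteristics are compared with those of caregivers who stay, because of concern about non-random attrition. No such check is planned for ordinary loss.
- **Tests (same section).** Independent-sample t tests are planned before the intervention. Independent and paired t tests, Mann-Whitney tests and paired rank-sum tests are planned after it. No covariate or baseline adjustment is mentioned.
- **Group formation (Setting and Participants).** Groups follow the admission period: "children admitted from July to December 2025 will form the control group", and the same months of 2026 form the intervention group.
- **Third assessment (Follow-Up Assessment).** One month after discharge, by telephone and web questionnaire: "The same validated instruments used during hospitalization will be used to measure caregiving preparedness, caregiving capacity, self-efficacy, and depression, anxiety, and stress". The Abstract mentions only the two in-hospital questionnaires.
- **Sample size (Setting and Participants).** The parameters are "α=.05, 1 – β=0.8, and effect size=0.5", which give 128. A 10% allowance for loss raises this to 142, split equally at 71 per group.

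**The concern.** Because deletion is written down as the rule, this is a choice the protocol has made and not a detail left to a fuller plan.

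The design gives reasons why loss might differ between groups. The cohorts are a year apart, and only the intervention group receives one-to-one coaching by a dedicated researcher, which may affect retention. The second questionnaire is tied to a date 3 days before discharge, so an unplanned discharge could remove it. The third is remote. The protocol does not predict who will be missing, so these are plausible routes and not stated facts.

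If loss is related to baseline or outcome in one cohort and not in the other, the caregivers who remain are no longer comparable in the way the unadjusted tests need. Those tests have nothing to correct for it, and no sensitivity analysis would reveal it. Paired tests also exclude anyone who lacks one of the two scores.

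**Working it through.** **1. The plan's own sample size.** Inputs: two-sided alpha 0.05 (sidedness is not stated, but two-sided reproduces the figure), power 0.80, d = 0.5. The noncentral t calculation gives 63.77, so 64 per group and 128 in total, which matches. For loss, 128 / 0.9 = 142.2; the stated 142 agrees within rounding.

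**2. What deletion costs in power.** 71 per group recruited, d = 0.5, two-sample t test, group sizes rounded down:

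| Removed | Per group | Power |
|---|---|---|
| 10% | 63 | 79.5% |
| 20% | 56 | 74.6% |
| 30% | 49 | 68.8% |

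The planned 10% allowance is enough for 10% loss. Power falls below plan only if total removal, including excluded switchers or 1-month non-response, exceeds it.

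**3. Simple bias arithmetic.** Let m be the fraction lost in one arm, and D the amount by which those lost would have scored worse than those retained. The full-arm mean is (1 − m) × retained mean + m × lost mean, so the complete-case mean is too favourable by m × D. With D = 0.5 SD (assumed) and no selective loss in the other arm:

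- m = 0.10: 0.10 × 0.5 = 0.05 SD, a tenth of the design effect.
- m = 0.20: 0.20 × 0.5 = 0.10 SD, a fifth of it.

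Loss in the intervention arm flatters the intervention; loss in the control arm does the opposite.

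**4. When bias appears and when it does not.** Simulation with a true difference of 0.50 SD, 71 per group and about 20% missing. The baseline-to-post correlation of 0.5 or 0.7 and the loss mechanisms are assumptions.

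| Loss mechanism | Complete cases, unadjusted | Same cases, baseline-adjusted |
|---|---|---|
| Completely at random | 0.50 | 0.50 |
| Depends on baseline, same in both groups | 0.50 to 0.51 | 0.50 to 0.51 |
| Depends on baseline in the intervention group only | 0.59 to 0.63 | 0.50 |
| Depends on baseline, opposite directions | 0.68 to 0.75 | 0.50 |

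Deletion alone does no material harm in the first two rows. Deletion combined with unadjusted tests is harmful in the last two, where adjustment removes the bias. Loss driven by the unobserved outcome was not simulated; baseline adjustment cannot be relied on there.

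**5. Time points.** Three assessments are planned (about 3 days after admission, 3 days before discharge, 1 month after discharge). Data Analysis distinguishes only before and after the intervention, and lists no method that joins three occasions.

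**The case against.** The strongest reply is that each alarming reading depends on something the article does not say.

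- **That deletion biases the result.** A reader might infer this. It stands only as a possibility: the article gives no missingness mechanism, and random or equally selective loss leaves the difference intact. It is also wrong that deletion is unbiased only under missing completely at random.
- **That deletion is the culprit.** For baseline-dependent loss, the same complete cases with baseline adjustment recover the true difference. The weakness there lies in the combination with unadjusted tests.
- **That observed scores are thrown away.** This depends on whether removal is per participant or per test. Under per-test removal, a caregiver lost later still counts in the baseline comparison. Only paired tests necessarily need both scores.
- **That the 1-month data have no test.** A 1-month score is after the intervention, so the listed tests could be applied to it. What stands is that the time point is unnamed and no longitudinal method is given.
- **That the trial loses power.** About 14 of 142 caregivers (10%) is what the allowance already covers.
- **That item gaps could remove nearly half the questionnaires.** With 64 items (8 + 25 + 10 + 21) and 1% item non-response, 1 − 0.99^64 = 47% have at least one gap. This assumes independent gaps, an invented rate and deletion across all four scales together. At 0.2% it is 12%. Per scale at 1% it is about 8%, 22%, 10% and 19% for 8, 25, 10 and 21 items. These figures show only why the rule should say how gaps are handled.

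What survives is that a single deletion rule, with no assumption, adjustment or sensitivity analysis, is a weak choice for this design.

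**Conclusion.** The point holds as a risk that the plan leaves unguarded, not as a demonstrated bias. Deletion is the sole stated rule and is paired with unadjusted comparisons of non-randomised cohorts recruited a year apart, so the group difference can be biased if loss is selective differently by group.

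The illustrative size is 0.05 SD at 10% and 0.10 SD at 20% one-arm loss, if those lost would have scored 0.5 SD worse. The simulated 0.59 to 0.75 against a true 0.50 needs about 20% loss, twice the allowance, and mechanisms that the article neither states nor excludes. The documents do not support saying that the result will be biased, that the sample size is wrong, or that the 1-month scores cannot be analysed. The plan should be changed, because the weakness is real and cheap to remove.

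**What to change.** Replace the deletion sentence with the following.

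- **Main analysis.** A likelihood-based linear mixed model for each outcome with group, time and group × time, using all available assessments. Account for the baseline score and the baseline covariates already collected. State whether the baseline score enters as the first response or as a covariate, not both: with non-randomised groups the two can answer different questions.
- **Contrasts.** Report the group contrasts at pre-discharge and at 1 month from this model. Controls are offered the programme at their second admission, and its timing relative to the 1-month assessment is not stated. The model does not resolve this, so record for each control whether the programme came first.
- **Missing items.** Handle isolated gaps within each scale by a stated rule, not by removing the record.
- **Sensitivity analyses.** Keep the complete-case analysis, and add a delta-adjusted multiple imputation in which imputed scores are made worse by stated amounts, by arm, including the 0.5 SD used above. Say how scores are treated when they are no longer defined and not merely missing.

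**Cost.** Revised wording and modest extra analysis; mixed models are available in SPSS 26. The main analysis relies on missing at random, which is why the delta-adjusted analysis is needed. If the change is made before the intervention cohort is recruited (planned for July to December 2026), it precedes any comparative data.

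### Caregivers who ask to change group are dropped from the primary analysis, so the main comparison omits a self-selected subgroup, possibly unequally between the groups

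*Protocol article*

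**What the plan says.** Allocation is by calendar period (Methods, Setting and Participants): "children admitted from July to December 2025 will form the control group, and those admitted from July to December 2026 will form the intervention group". In the paragraphs after Figure 1, the article says that caregivers are not blinded to group. It also permits a change of group: "If family caregivers prefer to adjust their groupings, appropriate adjustments will be made based on their identified needs". This permission covers caregivers in both groups.

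The Data Analysis section fixes what happens to those who use it: "Participants who request to switch groups based on their preferences will be excluded from the primary analysis". What triggers exclusion is the request. The one stated response is that "we will summarize the baseline characteristics of these participants and compare them to those who remain in their originally assigned groups", with the aim to "assess the potential impact of nonrandom attrition on study validity". No outcome analysis that retains these caregivers is described.

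The Control Group section adds: "Participants in the control group will be offered an FCEM-based intervention regimen on their second admission". The sample size paragraph allows 10% for loss to follow-up and makes no separate allowance for excluded switchers.

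**The concern.** Admission period decides the group, and a caregiver cannot influence it. That is the main protection a non-randomised, period-based comparison has. The switching rule gives it up: unblinded caregivers can remove themselves from the primary analysis by expressing a preference.

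The outcomes are preparedness, capacity, self-efficacy and distress. A wish to be in the other group is plausibly related to all of them, so those who remain need not represent the group they were enrolled in. If requests are more common, or differently motivated, in one group, the difference between groups mixes the effect of the programme with the effect of who left. A table of baseline characteristics shows whether movers look different; it does not correct the estimate.

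The excluded caregivers also come on top of ordinary loss to follow-up, which is all the sample size allows for.

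**Working it through.** **Inputs from the protocol article** (Setting and Participants): α = 0.05, power 0.80, standardised effect 0.5, 128 before loss, 10% loss, 142 in total, 71 per group.

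**Assumptions, because the article gives no figures:** the share of controls who switch, q (10% and 20%); no switching in the intervention group; and how strongly moving is related to the outcome.

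**1. The plan's own figure.** A two-sample t test, two-sided α = 0.05, d = 0.5 and power 0.80 needs 63.77, so 64 per group, or 128. This matches. 128/0.9 = 142.2, against 142 stated, which is a rounding matter only. With 10% loss, 71 × 0.9 = 63.9 caregivers per group remain and power is 0.80.

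**2. Shift in the control mean.** If a fraction q leaves according to a normally distributed propensity that correlates ρ with the outcome, the mean of those who stay shifts by ρ × φ(z_q)/(1 − q) SD.

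| q | φ(z_q) | ceiling, ρ = 1 | ρ = 0.5 | ρ = 0.5 as share of 0.5 SD |
|---|---|---|---|---|
| 10% | 0.1755 | 0.1755/0.9 = 0.195 | 0.10 | about 20% |
| 20% | 0.2800 | 0.2800/0.8 = 0.350 | 0.17 | about 35% |

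The ceiling requires the movers to be exactly the caregivers with the most extreme later outcomes, so it is a bound and not an expectation.

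**3. A milder assumption.** The shift also equals q × (mover–stayer difference in SD). For a difference of 0.5 SD this gives:
- 5% switching: 0.05 × 0.5 = 0.025 SD
- 10% switching: 0.10 × 0.5 = 0.05 SD
- 20% switching: 0.20 × 0.5 = 0.10 SD

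**4. Direction.** If controls with the worst scores leave, the remaining controls look better and the benefit is understated. If controls with the best scores leave, the benefit is overstated. At ρ = 0.5 (non-central t, numbers as in step 5):
- Overstatement with no true effect: two-sided type I error rises from 5% to about 8% (q = 10%) or 15% (q = 20%).
- Understatement with a true effect of 0.5 SD: power falls to about 59% or 40%.

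**5. Loss of numbers alone.** Controls retained are 63.9 × 0.9 = 57.5 or 63.9 × 0.8 = 51.1, against 63.9 in the intervention group. Power at d = 0.5 is 0.78 or 0.75.

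**6. Cost of keeping movers in their admission-period group.** If every control who moves receives the full effect, the expected difference is 0.5 × (1 − q), that is 0.45 or 0.40 SD. With 63.9 per group, power is about 0.71 or 0.61.

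**The case against.** The strongest reply is that the authors saw the problem. They name the attrition as nonrandom and plan to compare movers with stayers. That comparison covers baseline characteristics, including demographics, and nothing rules out baseline questionnaire scores. The number of switchers may be tiny, and the offer of the programme at second admission weakens a control caregiver's reason to ask. Step 6 also shows that, before any selection bias is counted, exclusion loses less power than retaining crossovers. All of this stands. It bears on the size of the problem and the choice of remedy, but does not make the excluded group any less self-selected.

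A reader might infer three stronger things that the documents do not support.

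- **That the exclusions fall mostly on the control group.** This is plausible, since only controls go without the programme during the study admission and they know it. But the rule applies to both groups and no rate or split is given.
- **That exclusion is tied directly to the outcomes because adjustments follow caregivers' identified needs.** That phrase describes how an adjustment is made. Exclusion follows from a preference-based request, so the link to outcome is likely but inferred.
- **That the planned 80% power will not be met.** This holds only if total losses exceed the 10% allowance, which nothing in the article establishes. Even at the assumed rates the fall is modest.

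**Conclusion.** The point holds in this form: the stated rule makes the primary comparison conditional on a post-enrolment choice by unblinded caregivers, and the planned baseline comparison does not repair it. The direction of bias cannot be known in advance.

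Its size depends on an unknown switch rate. It is negligible with few switchers. It reaches about 0.10 to 0.17 SD, or a fifth to a third of the design effect, if 10% to 20% of controls switch and moving correlates 0.5 with the outcome. About half that applies if movers differ from stayers by 0.5 SD. Nothing in the plan caps the number of switches. The effect on power through lost numbers is secondary. The sample size calculation itself is sound.

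**What to change.** 1. Delete the sentence in Setting and Participants that allows groupings to be adjusted. The right to withdraw and the offer of the programme to controls at second admission stay as written. This is the main part of the fix.
2. In Data Analysis, define the primary analysis as every enrolled caregiver with outcome data, analysed in the group of the child's admission period whatever was received.
3. Keep collecting outcomes from anyone already allowed to move, and report switch requests by group.
4. Keep the analysis that excludes movers as a sensitivity analysis, with the baseline comparison alongside it.

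The cost is protocol wording and an ethics notification. The statistical downside is that retained crossovers dilute the estimate: slightly if few, materially if many (step 6). That is why ending switching comes first and the analysis rule serves to cover those already moved. None of this makes a comparison of cohorts recruited a year apart equivalent to a randomised one; it only removes an avoidable selection step.
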